#### Disease Severity

If possible, disease severity will be categorized. For participants with asthma, it will be step 1-5, as per the GINA guidelines. In patients with COPD, this will be categorized as A-D using the GOLD guidelines with the severity of airflow limitation based on current or last available spirometry results within the last 12 months combined with their CAT score and exacerbation history. For participants with respiratory conditions other than asthma and COPD, the number of exacerbations in the last 12 months and lung function, if available, will be used to determine disease severity.

#### Spirometry

Spirometry will be conducted using a spirometer conforming to American Thoracic Society/European Respiratory Society standards, as specified by the manufacturer’s instructions. Participants will inhale rapidly and completely from functional residual capacity, then exhale in an initial forced exhalation and continue exhalation until the end of the breath. FEV_1_ (L), FVC (L), and FEV_1_/FVC ratio will be recorded. FEV_1_ and FVC will be documented as both absolute values and as a percentage of the predicted value [18]. A minimum of 3 tests will be performed, with 2 tests within 100 mL or 5% of each other. Spirometry results taken within the last 12 months will be recorded if the current results are unavailable. Spirometry will only be performed and recorded in the CRF if it is required as part of the participant’s routine care standard care (eg, as part of a clinical appointment). For participants recruited outside of the clinical setting, spirometry will not be performed as part of the study assessment.

#### Previous Inhaler Technique Training

The date of the participants’ most recent inhaler technique assessment for the device being observed during the study visit will be recorded in the CRF, along with the cadre of the person by whom it was assessed (eg, nurse, pharmacist, physiotherapist, or doctor). We will also record which inhaler device the participant is observed using and how long they have been using this device for.

#### SPUR Profiling Tool

The SPUR profiling tool summarizes the understanding of patient behavior and their health beliefs into four drivers: social (ie, support from family and society), psychographic (ie, beliefs on identity and reactance to authority), usage (ie, financial or personal barriers), and rational (ie, decisions based on burdens to overcome and the gravity of their condition). It has been developed by the company Observia and is a comprehensive way of assessing an individual’s level of behavioral and adherence profile. The tool is designed to be dynamic, so participants progress through the questions based on the responses to previous questions, which takes approximately 7 minutes to complete and is completed using an iPad, tablet, or smart phone with a user-friendly interface. Participants will be asked up to 17 questions, and the SPUR output will be calculated. The first 4 questions are not directly related to the participants’ situation but are hypothetical situations of other patients, which is called the Vignette technique [19]. Responding to the circumstances of a third party (ie, other patients) not only allows for stronger reactions in a less threatening way but also elicits starting assumptions as a primer for the rest of the assessments. The results of the SPUR profile will not be disclosed to the patient and only be recorded in the CRF and stored by Observia, as this study does not intend to inform patient management decisions.

The data collected will be anonymized with the participants’ unique study number and will only be collected for the purpose of the study. This profiling tool will be used for each participant in the presence of a member of the research team. Observia will host the data collected during the study by Avenir Télématique, an accredited health care data hoster based in France. Observia and Avenir Télématique both act in compliance with the General Data Protection Regulation requirements.

#### Device-Specific Error Frequency

Each of the device-specific checklists, devised from manufacturers’ guidelines, includes steps to follow as recommended by manufacturers to achieve a good inhaler technique. Each step carried out by the participant will be recorded as a dichotomous yes or no answer. There will also be space on the checklist to record additional errors that may not have been recognized.

#### Error Rates

The error rates recorded for each device type will be compared with errors made in other devices in the statistical analysis.

### Inhaler Technique Observation and Intervention

Once consent has been obtained, participants will be invited to a suitable clinic room to ensure privacy and a controlled environment with no time pressure. They will be accompanied by a member of the study research team, and the same person will both assess and correct any identified errors in the inhaler technique. The study team members will also record all relevant study data into the CRF. The participants will be asked to demonstrate their inhaler technique using a single-use placebo inhaler device. This is standard clinical practice, and placebo devices, which are identical to the inhaler, are available for all inhaler device types. The technique for using a placebo device is identical to how they would use their inhaler.

The member of the study team will first observe the participant’s inhaler technique using the placebo device for the inhaler that the participant has been prescribed. Any errors in the inhaler technique will be recorded against the device-specific checklist formulated using the manufacturer’s guidelines. This checklist, unique to each inhaler device, includes specific recommended steps to be followed to achieve an optimum inhaler technique, along with any errors in the technique that have been observed.

Participants who are observed to make errors with their inhaler technique will be given feedback by the study team member, and any errors will be highlighted and discussed. The correct technique will be demonstrated by the study team member, with emphasis on correction of the errors, and the participant will then be asked to repeat the demonstration of the inhaler technique to ensure that the errors have been corrected. This method of inhaler technique correction is part of standard clinical practice. A written handout with the correct technique for that device will also be issued to the participant, so that they can refer to this to continue to implement the correct technique.

If a participant is observed making repeated errors using their device, despite inhaler technique correction, a more suitable inhaler device will be considered. If it is possible to obtain a prescription from a qualified health care professional for an alternative, more suitable device, then this device will be issued during the study visit. The participant will be taught how to use the new device and will be asked to demonstrate the correct technique as per standard clinical practice. Observations with ITE will be recorded in the participants’ CRF for the initial device only. A letter will be sent to the participants’ GP, informing them that a new inhaler device has been issued, with a request to add this to their future repeat prescriptions. If it is not possible to issue an alternative device, a letter will be sent to the participants’ GP recommending a change to a more suitable device, and the participant will require training in the use of this new device. If a participant is participating in another research trial, they will be encouraged to communicate any change in device type or medication with the investigators of the other trial.

If a participant has been prescribed and uses more than 1 inhaler device type, observation and correction of only one device type will be carried out.

To ensure that each member of the study team involved in the inhaler technique observation has the necessary expertise and to ensure standardization across device technique assessment, all members of the study team will attend regular training sessions that will continue every 3 months throughout the study to ensure that competencies have been maintained. Study investigators will have to demonstrate the perfect inhaler technique for each device to be deemed competent. A standard operating procedure for the correct inhaler technique for each device will be produced, and records of competencies will be kept in the study site file.

### Discontinuation or Withdrawal of Participants From the Study

Participants will be assured that they can withdraw from the study at any time and that they do not have to give reasons for their withdrawal. Participants who do not wish to have their inhaler technique observed and corrected will not be recruited into the study. Potential participants approached within the clinical setting of Queen Alexandra Hospital (Portsmouth), but who do not wish to be recruited into the study, will have their inhaler technique observed and will be reeducated as necessary as per normal clinical practice. They will be assured that withdrawing from the study will not affect their ongoing medical care in any way.

### Procedures for Data Management

The observation and correction of inhaler technique is part of normal clinical practice, and enrollment in the study will not be documented in the participant’s medical notes. Completed CRFs will be stored in a secure location at Queen Alexandra Hospital and can be accessed only by the research staff. All data will be recorded on paper CRFs.

The SPUR profiling tool will be administered using an iPad, tablet, or smart phone. The anonymized data will be hosted by Avenir Télématique, an accredited health care data hoster based in France. The data collected will only be collected for the purpose of this study. Observia and Avenir Télématique both act in compliance with the General Data Protection Regulation requirements.

### Data Management

A bespoke database will be created for this study. Data will be entered, and 10% of records will subsequently be randomly checked against the original CRF. Further verification will be performed according to the frequency and pattern of the errors. The research team and the Portsmouth Technology Trials Unit will carry out all data verification.

### Data Analysis

#### Overview

Errors made at each step in each specific device will be tabulated, so that errors and error frequencies can be recorded for each inhaler device against predefined checklists based on the manufacturers’ guidelines. As a minimum of 50 participants are to be recruited for each inhaler device type, there may be a difference in the number of participants in each inhaler group. To reduce bias of over- or underselection, analysis will be restricted to 50 participants using each inhaler device, and participants will be randomly selected for the analysis.

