#### Primary Objective

The primary objective of this study is to assess the prevalence of device-specific ITE in 13 different devices, using the manufacturers’ guidelines.

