### Sampling and Sample Size

A minimum of 650 participants will be recruited for the study. To ensure an adequate sample size for each of the 13 different device types, a minimum of 50 participants will be recruited for each device group. Owing to the wide variety of devices involved in the study, it was not possible to conduct a power calculation because the device error frequency is known to be disparate among the inhalers involved. On the basis of existing recruitment numbers in published ITE trials [15], alongside the expert clinical opinion from within the protocol development team, a minimum of 50 participants using each device type was felt appropriate to provide a reasonable chance to identify a range of errors.

Potentially, participants may be using several different inhaler device types, so there could be a choice of device type to observe. Throughout the study, the study team will closely monitor the number of participants recruited using each of the 13 device types; therefore, to ensure that the risk of selection bias is distributed equally across all device types, the least commonly recruited device type will be observed in each participant.

Careful consideration has been afforded to ensure that adequate numbers of participants are recruited in all 13 device types included in the study. We will have access to more than 70,000 patients across the Wessex region using participant identification center ITE. Examination of primary care databases will identify those using the inhaler types included in this study, and invitations to participate will be sent to ensure recruitment across all device types.

Recruitment will last for up to 24 months and will not cease at the recruitment of 50 participants in each group, allowing sample sizes greater than this figure.

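### Capping the analysis at a random 50 participants per device removes no selection bias from device-specific results and loses precision wherever more than 50 are recruited

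*Protocol article*

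**What the plan says.** All of this is in the protocol article.

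- **Sampling and Sample Size** sets the target as a floor: "A minimum of 650 participants will be recruited for the study", and "a minimum of 50 participants will be recruited for each device group". Recruitment "will not cease at the recruitment of 50 participants in each group, allowing sample sizes greater than this figure". There is no formal power basis: "it was not possible to conduct a power calculation because the device error frequency is known to be disparate among the inhalers involved". For users of several devices, "the least commonly recruited device type will be observed in each participant".
- **Data Analysis, Overview** expects device groups of different sizes and responds with a cap: "analysis will be restricted to 50 participants using each inhaler device, and participants will be randomly selected for the analysis". The purpose it gives for this is "To reduce bias of over- or underselection". No full-sample analysis is mentioned, and no other use is given for the participants left out.
- **Primary Objective** is to "assess the prevalence of device-specific ITE in 13 different devices, using the manufacturers’ guidelines". **Primary Analysis** compares the number of errors across devices by one-way ANOVA, or by Kruskal–Wallis if the distribution makes ANOVA unsuitable.
- **Secondary Analysis** compares the number of errors across CAT, exacerbation, GINA, GOLD and training categories and describes no adjustment for device.

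**The concern.** The two sections pull against each other. One recruits beyond 50 so that larger samples become available; the other makes 50 the most that can be analysed. The reason given for the cap is bias, but a random draw from people already recruited cannot change who was recruited. Selection acts upstream, through the recruitment channels and the choice of which device to observe.

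At stake are the precision of every device-specific prevalence where recruitment exceeds 50, the power of the between-device comparison, and the chance of seeing uncommon errors, which is the article's own justification for 50 per device. Participants outside the draw would have consented and been observed without contributing to the analysis.

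**Working it through.** **Inputs.** From the article: 13 devices, a minimum of 50 each, exactly 50 analysed per device. Assumed, because the article does not give them: numbers recruited above 50, error prevalences, error-count distributions, and 95% intervals (two-sided 5% level).

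**Plan's own figure.** 13 × 50 = 650, which reproduces the stated minimum. There is no power calculation to reproduce.

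**Bias.** For a simple random subset, E(subset mean) = mean of the recruited group. Suppose true prevalence is 50% but selective recruitment yields a group at 35%. Simulated estimates were 35% from the full group and 35% from the random 50. The 15-point bias is untouched.

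**Precision within a device.** Half-width = 1.96 × √(p(1−p)/n). Analysing 50 of n recruited multiplies the variance by n/50 and the width by √(n/50).

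| Recruited n (assumed above 50) | Half-width using all, p = 50% | Half-width using all, p = 10% | Cap widens the interval by |
|---|---|---|---|
| 50 | 13.9 points | 8.3 points | 1.00 |
| 75 | 11.3 | 6.8 | 1.22 |
| 100 | 9.8 | 5.9 | 1.41 |
| 150 | 8.0 | 4.8 | 1.73 |

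At n = 60 the factor is √1.2 = 1.10.

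**Noise from the draw.** With 150 recruited and 50% of them making an error, the SD across possible draws of 50 is √[(0.25/50) × (1 − 50/150) × 150/149] = 5.8 points.

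**Uncommon errors.** For an error made by 2% of users (assumed), P(seen at least once) = 1 − 0.98ⁿ: 64% at n = 50, 87% at 100, 95% at 150.

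**Between-device comparison.** This was simulated with 4,000 runs, Poisson error counts, six devices at 150 and seven at 50, so 1,250 recruited, 650 analysed and 600 unused. With device means between 1.7 and 2.3:

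- The estimated mean for a 150-participant device was 1.70 with and without the cap.
- Its standard error was 0.188 capped and 0.107 on all data.
- Kruskal–Wallis power was 32% capped and 74% on all data.
- With no true difference, type I error was 5.4% capped and 4.6% on all data.

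**Pooled analyses.** Keep those sizes and assume 30% prevalence in the six large devices and 60% in the seven small ones.

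- As recruited: (900 × 0.30 + 350 × 0.60)/1,250 = 38.4%.
- Capped: (6 × 0.30 + 7 × 0.60)/13 = 46.2%, SE 1.87 points.
- All data, devices equally weighted: the same 46.2%, SE 1.58 points.

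**Unequal variances.** Normal data under the null, same group sizes, small groups with twice the SD of the large ones. Classical ANOVA had type I error of about 28 to 30% over repeated simulations on all data, against 7% capped; Welch ANOVA on all data gave 5%. Kruskal–Wallis gave 14% on all data against 4 to 5% capped. With SD ratios of 1.25 and 1.5, ANOVA on all data gave 11% and 18%, and Kruskal–Wallis 8% and 10%. With the larger SD in the large groups, both tests became conservative (1 to 3%).

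**The case against.** The case for the cap has real content.

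- **It equalises device mix.** The secondary comparisons pool devices whose error frequencies the article itself calls disparate. Fixing 50 per device stops an over-recruited device from dominating, and this is a plausible reading of over- or underselection. This stands: the cap is not without purpose. But it changes what is being estimated rather than correcting selection, and equal weighting on all data reaches the same target with a smaller standard error.
- **It protects the planned tests.** Checklists are device-specific, so unequal variances across devices are plausible, and equal group sizes keep classical ANOVA close to its nominal level. This also stands. A reader might infer that the restriction can be deleted and the planned tests left as they are; the type I error rates above show otherwise. The point concerns test validity, not selection bias, and a robust test meets it without discarding data.
- **The loss is conditional.** The article gives no numbers above 50, and steering users of several devices towards the least recruited one, together with targeted invitations, should limit imbalance. This stands: the loss may be small, and is nil for a device that ends at 50.
- **The draw procedure and seed may be in a fuller plan.** Agreed, so their absence is not criticised here. A fixed seed would make the draw reproducible but would not recover the lost precision.

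**Conclusion.** The point holds for device-specific prevalence and for the between-device comparison. There the random cap removes no selection bias and multiplies the variance by n/50 in any device with more than 50 participants. The interval is 1.22 times wider if 75 are recruited and 1.73 times wider if 150 are; those recruitment figures are assumptions.

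Two stronger readings are tempting and not supported. One is that the cap achieves nothing anywhere: it does equalise device mix in the pooled analyses, only inefficiently. The other is that it undermines the primary analysis: an analysis of 50 per device has the size the design called for and remains valid for the recruited population. What is lost is efficiency, by an amount that cannot be known from the article. The point is a should-fix.

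**What to change.** 1. Replace the restriction in the Data Analysis overview with analysis of all eligible observed participants for each device, with device-specific confidence intervals.
2. In Primary Analysis, compare devices with a method robust to unequal variances, such as Welch ANOVA or a count model with robust standard errors.
3. In Secondary Analysis, stratify or adjust the pooled comparisons by device, or weight the 13 devices equally where an overall figure is wanted.
4. If a 50-per-device draw is still wanted, keep it only as a sensitivity analysis with a prespecified seed.

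No new data are needed. The cost is a change of primary test, device stratification in the secondary analyses, and slightly more analysis work. Items 2 and 3 should accompany item 1, because removing the cap alone would expose the planned ANOVA to unequal variances and let the recruited device mix drive the pooled results.

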#### Summary Statistics

Summary statistics will be presented for all the background characteristics. The proportion of participants for all background variables will be presented. The information will be available as described in the following sections.

#### Primary Analysis

The primary analysis will comprise a comparison of the number of errors made for each inhaler type. As the number of errors is unlikely to be normally distributed, both mean and median values will be presented in all cases. One-way analysis of variance (ANOVA) will be used to determine whether there is a significant difference between the number of errors per inhaler type. If this parametric test is inappropriate based on the distribution of the number of errors, the Kruskal–Wallis (ranked ANOVA) will be used instead.

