#### Secondary Objectives

The secondary objectives are as follows:

To assess whether the frequency of ITE are associated with participant demographics, respiratory diagnosis, and comorbidities; disease control as measured by questionnaires, such as Asthma Control Questionnaire (ACQ) for asthma and COPD Assessment Tool (CAT) score for COPD, and participant clinical characteristics including exacerbation frequency within the past 12 months; length of time a participant has been using the observed inhaler, along with previous device-specific inhaler technique training (if and when previous training has taken place and given by whom); and levels of behavioral and adherence risk profile as measured by the social, psychographic, usage, and rational (SPUR) profiling tool (Observia).To assess the user error frequency at each step in the device-specific guidelines.To compare user error rates among device types.

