### Eligibility Criteria

Participants will be drawn from a range of clinical conditions affecting adults that use an inhaler device. The inclusion and exclusion criteria are presented in Textbox 1.

Inclusion and exclusion criteria.

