**Inclusion criteria**
Participants must be aged ≥18 years.Participants should have been prescribed (by a doctor or health care professional) 1 of 13 inhaler device types for an airways condition (Accuhaler, Autohaler, Breezhaler, Easi-breathe, Easyhaler, Ellipta, Genuair, Handihaler, Nexthaler, pressurized metered-dose inhalers, pressurized metered-dose inhalers plus spacer [eg, Aerochamber or Volumatic], Respimat, and Turbohaler).Participants should be able to provide written informed consent.

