#### Potential Benefits or Risks of Study Participation

By participating in this study, participants who are observed making errors with their inhaler technique will have these errors highlighted and will be reeducated. This is a beneficial outcome for participants’ self-care and management and ensures that they maximize drug delivery from their inhaler.

This study analyzes a wide variety of inhaler devices and will help provide a clear picture of the inhalers that are associated with the most errors. Understanding this information is important in the context of managing lung conditions, from treating patients in primary care through to feeding this information back to device manufacturers.

Any risks to the participants have been carefully considered. Participants found unable to use the inhaler device they have been prescribed will have an alternative device issued if possible, or a letter will be written to their GP with the recommended new device as per clinical practice.

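### The only planned comparison between the 13 inhalers is unadjusted, so it can describe each device's users but cannot separate the device from its users; a prespecified adjusted model should be added

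*Protocol article*

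**What the plan says.** Primary Analysis states the aim and the test. "The primary analysis will comprise a comparison of the number of errors made for each inhaler type". Then: "One-way analysis of variance (ANOVA) will be used to determine whether there is a significant difference between the number of errors per inhaler type". If the distribution makes that test unsuitable, "the Kruskal–Wallis (ranked ANOVA) will be used instead". Neither test carries a covariate.

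The groups are formed by prescribing. The inclusion criterion reads "Participants should have been prescribed (by a doctor or health care professional) 1 of 13 inhaler device types for an airways condition", and Eligibility Criteria adds "Participants will be drawn from a range of clinical conditions affecting adults that use an inhaler device". Under Sampling and Sample Size, someone who uses several devices is observed on whichever type has recruited fewest people so far.

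The Objectives overview calls user characteristics possible determinants of poor technique. Secondary Objectives begins "To assess whether the frequency of ITE are associated with participant demographics, respiratory diagnosis, and comorbidities" and goes on to disease control, time on the device, previous training and the SPUR profile. These data are collected: age, gender, diagnosis and comorbidity under Participant Clinical Characteristics, and under Previous Inhaler Technique Training "We will also record which inhaler device the participant is observed using and how long they have been using this device for".

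Secondary Analysis tests background measures one at a time against the number of errors. None is combined with device.

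On the use of the results, Potential Benefits or Risks of Study Participation says the study "will help provide a clear picture of the inhalers that are associated with the most errors", and mentions passing this back to device manufacturers.

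**The concern.** Because device is not allocated at random, the 13 groups may differ in age, diagnosis, comorbidity and experience. If any of these affects technique, the difference in mean errors between two devices mixes two things: how hard the device is to use, and who uses it. A test with device as the only factor cannot tell them apart, and the rank-based fallback has the same limit.

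Two features of the design bear on this. The least-recruited rule steers multi-device users towards the rarer devices, which is one reason within the protocol why groups could differ. The random selection of 50 participants per device (Data Analysis, Overview) equalises group size but leaves each group's case mix unchanged in expectation.

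At stake is the reading of the main result. An inhaler could be reported to its manufacturer as error-prone because its users are older or have more comorbidity. A real device difference could equally be masked if case mix runs the other way.

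**Working it through.** **The plan's own figure.** 13 devices × 50 participants = 650, the stated minimum. It is a product, not a power-based number. The protocol gives no error rate, standard deviation, effect size or significance level, so the size of any case-mix effect has to be illustrated with assumptions.

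**Assumed inputs (none from the documents, apart from 13 × 50).**
- Errors per participant follow a Poisson distribution with mean 2 + d·x.
- x is a yes/no user characteristic adding d = 0.5 or 1 error.
- The prevalence of x rises in equal steps across the 13 devices, from 0.5 − s to 0.5 + s, with s = 0.2 (30–70%) or s = 0.3 (20–80%).
- Given x, device has no effect. Test level 5%.

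**Spurious difference between the extreme devices:** 2·s·d, that is 0.2 and 0.4 errors for s = 0.2, and 0.3 and 0.6 errors for s = 0.3 (d = 0.5 and 1).

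**Simulation, 2,000 studies per setting, share rejecting at 5%:**

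| Prevalence of x | d | One-way ANOVA | Kruskal–Wallis | Device test with x in the model |
|---|---|---|---|---|
| 50% in all | 0.5 | 5.0% | 4.7% | 5.2% |
| 50% in all | 1 | 5.9% | 5.6% | 5.7% |
| 40–60% | 0.5 | 4.5% | 5.0% | 4.9% |
| 40–60% | 1 | 7.3% | 7.4% | 6.0% |
| 30–70% | 0.5 | 8.2% | 7.7% | 5.1% |
| 30–70% | 1 | 18.5% | 17.3% | 4.9% |
| 20–80% | 0.5 | 12.8% | 12.2% | 5.2% |
| 20–80% | 1 | 42.2% | 40.0% | 4.8% |

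The Monte Carlo standard error is about 0.5 points at 5% (√(0.05·0.95/2000)) and 1.1 points at 42%.

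**Closed-form check of the ANOVA column.** The non-centrality is λ = 50·Σ(μᵢ − μ̄)²/σ². With 13 equal steps, Σ(μᵢ − μ̄)² = d²·(s/6)²·182. The average within-device variance σ² is the mean of 2 + d·pᵢ + d²·pᵢ(1 − pᵢ).
- s = 0.2, d = 1: Σ = (0.2/6)²·182 = 0.202; σ² = 2.734; λ = 50·0.202/2.734 = 3.70. A non-central F with 12 and 637 df gives rejection in 18.1%.
- s = 0.3, d = 1: Σ = 0.455; σ² = 2.715; λ = 8.38; rejection 41.4%.
- For d = 0.5 the same steps give 8.1% (s = 0.2) and 13.0% (s = 0.3).

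These agree with the simulation.

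**The case against.** The strongest reply is that this is a prevalence study. Primary Objective is the prevalence of errors by device, and comparing devices is listed only under Secondary Objectives. For the question of how many errors users of device A make compared with users of device B, the unadjusted comparison is the right one. In the illustration the group means really do differ, because the user factor differs, so rejecting equal means is correct for the hypothesis as the protocol states it. The rates above count as errors only against a different null: no device difference among comparable users. All of this stands. It is why the unadjusted analysis should stay. It does not remove the point, because Primary Analysis makes the between-device test the main analysis and the stated use of the results goes beyond describing users.

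Three stronger readings are tempting, and the documents do not support them.
- A reader might infer that the protocol claims device differences independent of the users. It speaks only of association; the feedback to manufacturers invites the causal reading but does not state it.
- A reader might infer that the protocol expects these characteristics to drive errors, or that case mix is known to differ. It calls them possible determinants and sets out to assess whether they are associated; it gives no data on imbalance. With a 40–60% spread the excess rejection is nil to about 2 points.
- A reader might want the one-way test replaced by a model containing every recorded determinant. That goes too far. Under Inhaler Technique Observation and Intervention, users with errors are retrained and those with repeated errors may be moved to another device. Time on the device and previous training may therefore be consequences of device difficulty, and adjusting for them could remove part of a real device difference or introduce selection bias.

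It is also fair that supporting models are often left to an analysis plan, which is not shown. Nothing here excludes one. The point is that the device comparison this document fixes is unadjusted.

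**Conclusion.** The point holds as a limit on interpretation that is cheap to remove. The planned test is valid for comparing the users of the 13 devices. It cannot separate the device from its users, and the characteristics recorded for every participant are never analysed jointly with device.

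The actual size of the bias cannot be derived from the documents and would be small if case mix turns out similar. Under the assumed inputs, with prevalence spreads of 30–70% to 20–80%, the unadjusted test rejects in about 8% to 42% of studies where device has no effect given the user factor; with the factor in the model the rate is about 5%. The top of that range needs both the larger factor effect and the wider spread. Kruskal–Wallis behaves almost identically, so the fallback gives no protection.

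**What to change.** Keep the unadjusted per-device description and test. Add to Primary Analysis:
- A prespecified regression of errors on device (count or binomial model with robust standard errors), adjusted for age, sex, respiratory diagnosis and comorbidity.
- The joint device test on 12 degrees of freedom (13 − 1), and adjusted device means with 95% confidence intervals, shown beside the unadjusted values.
- A statement that conclusions about the devices themselves rest on the adjusted results, while conclusions about their users rest on the unadjusted ones.
- A second, sensitivity model that also includes time on the device and previous training, labelled as such because these may follow from device difficulty. Disease control and exacerbations may be consequences of poor technique, so including them would need its own justification.
- For any device used almost only in one diagnosis, a comparison within that diagnosis rather than an adjusted mean that rests on extrapolation.

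The cost is analysis-plan wording and a little extra analysis, with no new data or participants. The downsides are a few model degrees of freedom out of 650, loss of records with a missing covariate (no imputation is planned), and wider intervals where diagnosis and device overlap little.
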